### Study population

This study will enroll individuals with confirmed infection with COVID-19 at selected Federal and Regional Hospitals irrespective of their differences (age, sex, symptoms, severity, and any other conditions). The patients' follow-up will be done strictly within the management adapted to their infection.

Individuals/patients in the study hospital or area will be eligible for inclusion if they meet the following criteria: (1) patient is admitted to selected treatment centers (Federal and Regional’s Hospitals) with COVID-19 confirmed by RT-PCR; and (2) consents to be enrolled in the follow-up study and provide all necessary information/data, blood sample, and nasopharyngeal swab for testing. Patients will be excluded if: (1) a subject deprived of freedom, subject under a legal protective measure; (2) refusal by a participant, parent or appropriate guardian or representative; (3) not willing to stay 12 months in the cohort in Ethiopia; (4) is already involved in the COVID-19 clinical trial or other interventional studies; (5) not capable of understanding or complying with the study protocol or provide consent; (6) anticipated transfer to another hospital that is not a study site within 72 h.

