**Methods:**

A multi-center cohort study design will be performed. Patients with confirmed COVID-19 infection admitted to selected treatment centers will be enrolled irrespective of their symptoms and followed-up for 12 months. Baseline epidemiological, clinical, laboratory and imaging data will be collected from treatment records, interviews, physical measurements, and biological samples. Follow-up data collection involves treatment and prognostic outcomes to be measured using different biomarkers and clinical parameters. Data collection will be done electronically using the Open Data Kit (ODK) software package and then exported to STATA/SPSS for analysis. Both descriptive and multivariable analyses will be performed to assess the independent determinants of the treatment outcome and prognosis to generate relevant information for informed prevention and case management. The primary outcomes of this study are death/survival and viral shedding. Secondary outcomes include epidemiological characteristics, clinical features, genetic frequency shifts (genotypic variations), and nutritional status.

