### Study design and period

A multi-center prospective open cohort study design on COVID-19 confirmed cases in Ethiopia conducted from December 01, 2020 to December 2021. Like many other disease-specific general open cohorts, such as in Framingham Heart Study and the Ethiopia Netherlands AIDS Research Project (ENARP) studies, the study intends primarily to measure the incidence of several epidemiological, clinical, virological, and immunological outcomes of COVID-19 cases [29, 30]. The cohort will be an unbiased extensive routine collection of clinical, radiographic, laboratory, and clinical management, virological, immunological and nutritional data, which helps to detect and address emerging research priorities without relying on a priori hypothesis.

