### Primary outcome and secondary outcomes

The primary outcome variables are treatment outcome (active cases, recovered, death or transferred for further treatment), recovery time, and duration of viral shedding (the time from the first positive RT-PCR results to the occurrence of the last positive RT-PCR results or negative RT-PCR results). The secondary outcomes include clinical symptoms and signs (major); co-morbidities; status at last follow-up (survival, severity, virus detection); laboratory biomarkers; duration of symptomatic phase, inpatient stay, ICU stay; viral loads; anti-SARS-CoV-2 antibody titer; imaging with results; therapeutic measures; plasma 25-hydroxyvitamin D concentrations; dietary history; micronutrient status (zinc and vitamin A); fasting blood sugar; weight, height, BMI; total cholesterol (TC), triglycerides (TG), HDL-C, LDL-C and body composition(waist circumference); genetic frequency shifts (genotypic variations); obstetric and gynecologic history; pregnancy status/test; clinical status; supplemental oxygen; non-invasive ventilation or oxygen delivery devices/ respiratory support. We will also collect confounding variables include socio-demographic variables (age, sex, education status); status cases at the time of enrollment; and months after the first positive test.

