### Data collection

Data collection will be done electronically using the REDCap software package and data documentation will be performed from a retrospective history of the patient and prospectively after treatment is finalized. Contact information such as home address and telephone number will be collected to facilitate follow up and for tracking defaulters of follow-up. For asymptomatic cases whose follow-up is undertaken at home, their home address, GPS coordinates and geospatial data for all participants will also be registered by trained data collectors (study nurse or doctor). Data will be gathered from patients and follow up cases through interviews by physicians/nurses at each treatment center using a questionnaire and standardized Case report form (CRF). Biological samples will also be collected at baseline and follow up when samples are taken in the context of care to meet the research objectives. Five-milliliter venous blood will be collected using a serum separator tube and 4 mL venous blood will be collected using a test tube containing anticoagulant. Viral load measures in a body fluid using Abbot and Rosh reagents and platforms will be measured. Phylogenetic analysis of SARS-CoV-2: genotyping of different types of SARS-CoV-2 from Ethiopian isolates under different settings will be done using a next-generation sequencer at Ethiopian Public Health Institute (EPHI). Imaging: chest x-ray, ultrasound scan, chest computed tomographic (CT) scans data will be retrieved if available. Laboratory tests for D-dimers, platelet count, PT, PTT, INR, D- Dimer, and serum ferritin will be measured.

The screening will be performed within the period between one to two days of admission to the hospital to review study inclusion/exclusion criteria; obtain prior medical and concomitant medication histories; perform a complete physical examination, including height, body weight, and vital signs (blood pressure, BP, heart rate, HR), Oxygen saturation (SpO2) with pulse oximetry; and collect a blood sample for laboratory testing on screening day.

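### Exclusion 5 has no exception for representative consent, which conflicts with enrolment at any age or severity and would probably lower the observed mortality

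*Protocol article*

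**What the plan says.** Four statements in the protocol article, Study population, bear on this point:

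- Enrolment is promised "irrespective of their differences (age, sex, symptoms, severity, and any other conditions".
- Inclusion 2 requires that the patient "consents to be enrolled in the follow-up study and provide all necessary information/data, blood sample, and nasopharyngeal swab for testing". No proxy is named.
- Exclusion 2 is "refusal by a participant, parent or appropriate guardian or representative".
- Exclusion 5 is "not capable of understanding or complying with the study protocol or provide consent". No proxy exception is given.

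On timing, the Data collection section states: "The screening will be performed within the period between one to two days of admission to the hospital".

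On outcomes, the abstract states: "The primary outcomes of this study are death/survival and viral shedding". The section on primary and secondary outcomes instead lists "treatment outcome (active cases, recovered, death or transferred for further treatment), recovery time, and duration of viral shedding". The sample size of 6,390 is built on a 28% death rate, a design effect of 2.5 and 20% loss to follow-up.

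**The concern.** In patients admitted with COVID-19, inability to understand or consent often results from the severity of the illness (sedation, ventilation, confusion) or from being a young child. These are two of the characteristics that the protocol says do not affect entry. An eligibility rule that acts on capacity therefore acts on severity, and severity predicts death.

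The death rate among enrolled patients would then describe admissions able to consent within a day or two of arrival, while the text presents them as patients of any severity. The analysis cannot repair this. The full-information likelihood and multiple imputation in the Data processing section address missing values and loss to follow-up among enrolled patients, and cannot reach patients who were never enrolled. A larger sample does not reduce the bias either.

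There is also a practical risk. Because the criteria point in two directions, sites have to decide for themselves whether a representative's agreement is enough.

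**Working it through.** **Step 1: the criteria side by side.** Take a ventilated patient whose representative agrees to participation.

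- Exclusion 2 is not met, because nobody has refused.
- Exclusion 5 is met, because the patient cannot understand or consent, and a representative's agreement is not listed as an exception.
- Inclusion 2 is not clearly met, because it asks for the patient's consent.

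As written, this patient is excluded. A young child with a willing parent is in the same position. Exclusion 2 covers only a proxy's refusal, and no criterion says that a proxy may consent. Yet a proxy's power to refuse makes sense only if a proxy may decide for some patients. The criteria are therefore not reconciled.

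**Step 2: the plan's own figure.** The article gives no precision margin, so 6,390 cannot be reproduced directly. It can be back-solved as a single-proportion precision calculation, assuming 95% confidence, with margin = 1.96 × √[0.28 × 0.72 / n]:

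- Loss handled as division by (1 − 0.20): n = 6,390 × 0.80 / 2.5 = 2,044.8, margin 1.95 points.
- Loss handled as multiplication by (1 + 0.20): n = 6,390 / 1.20 / 2.5 = 2,130, margin 1.91 points.

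A round 2-point margin would give 6,051 or 5,809. The implied margin of about 1.9 points serves here only as a yardstick for the bias.

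**Step 3: size of the selection effect.** Inputs:

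- p = 0.28, the planned death rate, taken as mortality among all admissions (an assumption).
- q = share of admissions excluded for incapacity. Not in the documents; assumed 2% to 15%.
- r = mortality among those excluded. Not in the documents; assumed 50% to 80%.

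Mortality among enrolled patients = (p − q·r)/(1 − q). The shift from p is therefore q·(p − r)/(1 − q), and the share of all deaths missed is q·r/p.

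Worked example, q = 0.05 and r = 0.60: (0.28 − 0.03)/0.95 = 0.2632, a shift of −1.68 points; deaths missed 0.03/0.28 = 10.7%.

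Shift in percentage points:

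| q | r = 28% | r = 50% | r = 60% | r = 80% |
|---|---|---|---|---|
| 2% | 0 | −0.45 | −0.65 | −1.06 |
| 5% | 0 | −1.16 | −1.68 | −2.74 |
| 10% | 0 | −2.44 | −3.56 | −5.78 |
| 15% | 0 | −3.88 | −5.65 | −9.18 |

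At the two ends, enrolled mortality is 27.6% with 3.6% of deaths missed (q = 2%, r = 50%) and 18.8% with 42.9% missed (q = 15%, r = 80%).

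The direction depends only on whether r exceeds p. Here r is the average over everyone excluded. Critically ill adults would raise it. Young children would lower it, since the Background describes death in children as extremely rare.

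**The case against.** The strongest reply is that exclusion 2 already shows proxies were foreseen, and that enrolment at any age implies parental consent. Read as a whole, exclusion 5 could simply mean that no valid consent can be obtained. A journal article also condenses the full protocol, and the mechanics of assent, proxy consent or deferred consent are commonly left to that document. This has force. A reader might infer that every patient who cannot consent personally is certain to be turned away, and the documents do not support that: exclusion 5 does not say personally, and exclusion 2 points the other way. What remains is that the printed criteria conflict, and that their literal application excludes these patients. That is a conflict in stated text rather than an omitted detail.

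Four further inferences are tempting and not supported.

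- Death is not the sole primary outcome. It stands beside viral shedding in the abstract, and it is one category of treatment outcome in the methods, beside recovery time and duration of viral shedding.
- The design section uses the word unbiased, but of the routine collection of data. It is not a claim that enrolment is unselected.
- Weaker associations of age, comorbidity or inflammation with death do not follow automatically. Selection on a baseline characteristic need not bias conditional associations in a correctly specified model.
- A larger loss of deaths at centres with more critical care cannot be shown, because the article gives no case-mix by centre.

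It is also fair to say that the effect may be small: at the low end of the assumed range it is under half a point, well inside the implied margin.

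**Conclusion.** The point holds as an unreconciled eligibility rule with a probable downward effect on the mortality estimate. Exclusion 5 and inclusion 2 leave no route for a patient without capacity. The enrolment promise and exclusion 2 imply that there is one.

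The size cannot be determined from the documents. Under the assumed shares and death rates the shift runs from about 0.5 to 9 points. It is close to the design's implied margin at a 5% share with 60% mortality (1.7 points) and exceeds that margin at a 10% share with 60% mortality (3.6 points). It is zero if the excluded patients die at the same 28% as everyone else, which is unlikely if most of them lack capacity because of critical illness. These figures rest on 28% being the mortality of all admissions and on exclusion 5 being applied literally. The change should be made, because it is inexpensive and because the analysis cannot recover patients who were not enrolled.

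**What to change.** Reword exclusion 5 so that it applies only when neither the patient nor a parent, guardian or legally authorised representative can give consent. Align inclusion 2 so that it accepts consent from the same persons. Both changes are subject to ethics approval, with the patient's own consent sought on regaining capacity.

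Report the number of screened admissions excluded for this reason, with age group and severity where ethics allows, so that readers can judge the selection.

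If representative consent is not permitted, restrict the statement about enrolment at any severity, and the mortality conclusions, to patients able to consent. That restriction and the screening counts remain feasible if enrolment has already begun.

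The cost is an ethics amendment, re-consent paperwork and a screening log at each participating centre. No change to the sample size or the analysis methods is needed.

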## Methods/design

### Aim and study setting

In this multi-site cohort study, we aimed to determine the natural history of the disease; clinical features and management, epidemiological characteristics, immunological, virological courses and treatment response of the disease, effects of diets on the nutritional status on the disease progression, effect of the disease on pregnancy and birth outcomes, and the effect of traditional/modern treatment on COVID-19 outcomes among patients admitted to treatment centers in Ethiopia. Therefore, the study findings will generate scientific data for a systematic understanding of natural history, epidemiological characteristics, clinical features, and management of COVID-19 which will, in turn, enable the country’s health sector to develop strategies to prevent and control the pandemic before it poses further health and socioeconomic crises. The research question of this study is “Do different individual host factors and environmental situations influence clinical, epidemiological, and viral outcomes of COVID-19 infection?”.

The study will be conducted in all Federal treatment centers, including Ekakotebe, Yekatit-12, St. Peter Specialized hospitals, SPHMMC, Millennium hall center in Addis Ababa, and Regional Hospitals including Mekelle, Semera, Bahir Dar, Adama/Mojo, Hawassa, Jijiga, Harar, DireDawa, Metekel or Benishangul Gumuz, and Gambela dedicated to COVID 19 treatment.

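### Exclusion 6 bars patients foreseen to move to a non-study hospital within 72 hours, although transfer is a category of the primary treatment outcome, so that category is depleted by an unknown amount

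*Protocol article*

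**What the plan says.** All references are to the Protocol article.

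- **Study population**, sixth exclusion: "anticipated transfer to another hospital that is not a study site within 72 h".
- **Study population**, opening statement: confirmed cases are enrolled "irrespective of their differences (age, sex, symptoms, severity, and any other conditions".
- **Primary outcome and secondary outcomes**: the first primary outcome variable is "treatment outcome (active cases, recovered, death or transferred for further treatment". Recovery time and duration of viral shedding are the other two.
- **Study design and period**: "the study intends primarily to measure the incidence of several epidemiological, clinical, virological, and immunological outcomes of COVID-19 cases".
- **Aim and study setting**: "The study will be conducted in all Federal treatment centers", together with a list of regional hospitals. A move between any of these is not touched by the exclusion.
- **Data collection**: "The screening will be performed within the period between one to two days of admission to the hospital", and "Contact information such as home address and telephone number will be collected to facilitate follow up".

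The article does not say why patients would be moved to a hospital outside the study, or how many would be.

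**The concern.** A proportion is only as good as its denominator. Here one category of the primary outcome is partly removed before counting starts, by a rule that depends on whether staff expected the event. Screening comes one to two days after admission, when some early transfers will already be planned. How many are planned by then may differ between hospitals, so the observed transfer share would partly reflect local foresight and referral practice.

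The other categories share that denominator. Patients about to leave the network need not resemble those who stay, so the proportions who die or recover could shift as well. Because the article describes no data on the excluded patients, none of the analysis methods it lists could correct for their absence afterwards.

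**Working it through.** **1. The two rules side by side.** Take a patient who moves to a hospital soon after screening, for more treatment.

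| Transfer | Destination | Enrolled? | Counted as transferred? |
|---|---|---|---|
| Foreseen, within 72 h | Non-study hospital | No | No |
| Unforeseen, within 72 h | Non-study hospital | Yes | Yes |
| After 72 h | Any | Yes | Yes |
| Any time | Study site | Yes | Yes |

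Only the first row is lost. The category is thinned, and the article gives nothing from which to say by how much.

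**2. Effect on the transfer share.** Let T be the true share transferred for further treatment and f the fraction of those screened out by exclusion 6. Both are assumed.

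Observed share = T(1 − f) / (1 − Tf)

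| T | f = 25% | f = 50% |
|---|---|---|
| 2% | 0.0150/0.9950 = 1.5% | 0.010/0.990 = 1.0% |
| 5% | 0.0375/0.9875 = 3.8% | 0.025/0.975 = 2.6% |
| 10% | 0.0750/0.9750 = 7.7% | 0.050/0.950 = 5.3% |

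This needs no assumption about mortality. It needs only that some of the patients screened out were moving for further treatment.

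**3. Effect on the death proportion.** Take the 28% from Sample size and sampling procedures as the source rate. Let t be the share of patients excluded and RR the risk of death in the excluded relative to those retained. Both are assumed.

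Retained death rate = 0.28 / (1 − t + t × RR)

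| t | RR 0.5 | RR 1 | RR 2 | RR 3 |
|---|---|---|---|---|
| 1% | 0.28/0.995 = 28.1% | 28.0% | 0.28/1.01 = 27.7% | 0.28/1.02 = 27.5% |
| 5% | 0.28/0.975 = 28.7% | 28.0% | 0.28/1.05 = 26.7% | 0.28/1.10 = 25.5% |
| 10% | 0.28/0.950 = 29.5% | 28.0% | 0.28/1.10 = 25.5% | 0.28/1.20 = 23.3% |

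The sign depends entirely on RR, and at RR 1 there is no shift at any t.

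**4. A yardstick.** The article states no precision target, so 6,390 cannot be reproduced from its stated inputs (28%, design effect 2.5, 20% loss). Working backwards with a two-sided 95% interval:

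- Loss applied by division: 6,390 × 0.8 / 2.5 = 2,044.8 effective patients; 1.96 × √(0.28 × 0.72 / 2,044.8) = 1.95 points.
- Loss applied by multiplication: 6,390 / 1.2 / 2.5 = 2,130; 1.96 × √(0.28 × 0.72 / 2,130) = 1.91 points.

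Against about 1.9 points, most of the shifts in step 3 lie inside sampling error. Only three cells exceed it: t = 10% at RR 2, and t = 5% or 10% at RR 3.

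**The case against.** The best defence is feasibility. Daily follow-up until discharge cannot continue at a hospital where no study staff work, and two of the three primary outcome variables, recovery time and RT-PCR-based shedding, need that follow-up. A telephone call can establish vital status but cannot replace a swab. Enrolling these patients therefore exchanges selection for missing data that may be informative. This stands, and it is the real cost of the change. It does not settle the matter. The design already follows people outside the sites for 12 months, allows for 20% loss, and plans multiple imputation and full-information maximum likelihood. Patients enrolled and partly observed can always be left out of an analysis; patients never enrolled cannot be put back.

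It is also fair to say that a general enrolment statement followed by six exclusions is not in itself a contradiction, and that exclusion 6 does not mention severity. The claim "The cohort will be an unbiased extensive routine collection of clinical, radiographic, laboratory, and clinical management" can be read as describing the breadth of data collected, so little weight rests on it. The case rests on the outcome definition and the incidence aim.

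Three stronger readings are tempting and are not supported:

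- **That the cohort is selected on its own outcome.** The rule acts on an expectation before enrolment and restricts eligibility. It does not condition on an observed outcome.
- **That it loses patients being escalated, so mortality is understated.** No reason for transfer is given. With all Federal centres in the study, escalation may well end at a study site, and those leaving the network could be milder cases.
- **That early transfers fall towards zero.** Unforeseen early transfers, and all early transfers to study sites, are still counted.

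Finally, patients moved before screening are missed with or without the exclusion, so removing it does not give complete capture of early transfers.

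**Conclusion.** The point holds as a narrow inconsistency between eligibility and outcome that should be corrected. Exclusion 6 lowers the observed transfer share for any further-treatment transfers it screens out. Under assumed inputs (a true share of 2% to 10%, a quarter to a half screened out), the cohort would show between 1.0% and 7.7%.

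The effect on deaths is undetermined in sign and size. Under the assumed ranges it runs from 4.7 points low (10% excluded, RR 3) to 1.5 points high (10% excluded, RR 0.5), and it is nil at equal risk. The recovery proportion may likewise shift, in an unknown direction. No number in the article is shown to be wrong by this, and no figure in the documents fixes T, f, t or RR.

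**What to change.** Drop exclusion 6. Enrol these patients at screening and record the date, reason and destination of any transfer as an event. Obtain vital status afterwards through the address and telephone details already collected. After transfer, treat viral shedding and recovery time as censored or missing, and add a sensitivity analysis that leaves out the patients whose early transfer was foreseen at screening. That analysis gives back the restricted cohort, so nothing is lost by enrolling them.

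Cost: a change to the eligibility wording, a few fields for the transfer event and for whether it was foreseen at screening, and incomplete RT-PCR, recovery-time and laboratory data for this subset. No study product is assigned in this observational cohort, so none requires their exclusion.

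If the sponsor keeps the rule, count the patients excluded under it with their severity at screening, and state that the transfer, recovery and death proportions apply only to patients not expected to leave the study network within 72 hours.
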